## Assessment of safety

Safety, tolerability and compliance will be assessed with 6 weekly assessments which consist of:

- 8 weekly dispensing of Vitamin D/ Placebo
- Pill count as measure of compliance
- Monitoring and recording of all adverse events
- Serum calcium and phosphate will be checked after 8 weeks of supplementation

### *Adverse Events (AE)*

Vitamin D dietary supplementation may be detrimental in persons already receiving an adequate intake through diet and exposure to sunlight. Minimum of 2000iu of Vit D3 is the recommended replacement dose for patients with vitamin D deficiency. No adverse events are anticipated for this study using 4000iu Vit D3 or placebo in women with documented vitamin D insufficiency.

Excessive intake of vitamin D (50,000 iu daily for a few months) can lead to development of hyperphosphataemia or hypercalcaemia. Associated effects include hypercalciuria, ectopic calcification, renal and cardiovascular damage. Symptoms of overdosage include anorexia, lassitude, nausea and vomiting, constipation or diarrhoea, polyuria, nocturia, sweating, headache, thirst, somnolence and vertigo. Hypersensitivity reactions can occur.

(Source: Martindale : The complete drug reference)

The 8 weekly dispensing of study meds will allow for monitoring and reporting of any unforeseen adverse event. Subjects are instructed to contact via phone for earlier review in event of AE or intolerance to study meds. Patient with intolerance of vitamin D leading to poor compliance will be excluded from trial.

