### *Subject withdrawal & drop-out*

Subjects are free to withdraw from the study at any time for any reason. Subjects may also be withdrawn from the study at any time at the discretion of the investigator.

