### *Procedures for handling withdrawal*

Subjects who withdraw or are withdrawn from the study should:

- Have the reason(s) for their withdrawal recorded
- Be asked about the presence of any AEs
- Be seen by an investigator and all final assessments will be performed and recorded
- Have study treatment returned.

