### *Treatment and follow up of AE*

Treatment of any AE is at the sole discretion of the investigator who should follow up subjects with AE until the event has resolved, until the condition has stabilised, the subject is lost to follow-up, or the adverse events are otherwise explained. Appropriate medical care should be arranged for the patient. Abnormal tests should be repeated until they return to baseline levels or an adequate explanation of the abnormality has been found. Any follow up information should be reported as soon as it becomes available.

- - - - - Treatment of over-dosage

Significant overdose of Vitamin D occurs with very high intake. In adults, toxicity occurs with more than 50,000 IU/day of Vitamin D for several months.

Suspicion of overdose will be referred to study doctor for further assessment.

Unblinding will be done at discretion of study doctor to allow further management.

- - - - - Pregnancy

Vitamin D at dose of 4000iu/ day is safe in for maintainence or prevention of Vit D deficiency and recommended in pregnancy ^24^.

However, as the study involves use of placebo, subjects who are found to be pregnant during screening will be excluded from further participation of trial. Hormonal changes during pregnancy may also alter glucose metabolism and potentially interfere with accuracy of results.

Only patient with no active plan to get pregnant again within 6 months of study participation will be recruited. In the event of unplanned pregnancy after randomization, treatment of subject will be unblinded. Pregnant subjects will be excluded from further participation in trial and referred for appropriate follow up according to local practice.

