## Criteria for stopping subject treatment

Subjects can withdraw consent from study at any time point without compromising care

Subjects who became pregnant during duration of study will be withdrawn and referred for follow up as per local practice

Subjects who are deemed inappropriate for further continuation at discretion of study co-ordinator will be withdrawn from study and reason documented

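### The protocol does not separate stopping study capsules from leaving the study, so women removed for intolerance or by discretion have no planned week-24 endpoint

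*Protocol*

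**What the plan says.** Four places in the protocol bear on what happens to a woman who comes off study capsules.

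- *Adverse Events (AE)*: "Patient with intolerance of vitamin D leading to poor compliance will be excluded from trial". The exclusion is from the trial, not only from the capsules.
- *Criteria for stopping subject treatment*: despite its heading, this section deals only with leaving the study. It covers withdrawal of consent, pregnancy, and a discretionary rule: "Subjects who are deemed inappropriate for further continuation at discretion of study co-ordinator will be withdrawn from study and reason documented".
- *Subject withdrawal & drop-out*: "Subjects may also be withdrawn from the study at any time at the discretion of the investigator".
- *Procedures for handling withdrawal*: this applies to "Subjects who withdraw or are withdrawn from the study should" and includes "Be seen by an investigator and all final assessments will be performed and recorded" in the same short list as "Have study treatment returned". It gives no date for those assessments.

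The primary criteria (*Assessment of efficacy*) are changes in OGTT glucose and insulin AUC and in HOMA-IR. The closing measurement is Visit 6, at the end of 6 months, shown as week 24 in the visit schedule. The Visit 6 text speaks of all subjects and does not mention withdrawn women. Section 10.3.1 analyses according to protocol and drops women who were not treated as intended or who lack efficacy data.

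**The concern.** Stopping a treatment and stopping follow-up are different events. When a protocol runs them together, the outcome goes missing because of something that happened after randomisation: tolerance, adherence or a staff judgement. The women left at week 24 are then a selected group, and the randomised comparison no longer protects against that selection.

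This is a matter of data collection and comes before any choice of analysis set. A statistical analysis plan can change who is analysed, but it cannot supply a week-24 OGTT that nobody took. An OGTT taken at an undated exit may follow a shorter exposure than the 6 months that the endpoint is meant to describe.

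**Working it through.** **Step 1. Routes off treatment, side by side.**

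| Reason | What the protocol provides | Week-24 OGTT provided for? |
|---|---|---|
| Intolerance with poor compliance (*Adverse Events (AE)*) | Excluded from the trial | No |
| Discretion (*Subject withdrawal & drop-out*; *Criteria for stopping subject treatment*) | Withdrawn from the study | No |
| Pregnancy (*Treatment and follow up of AE*) | "Pregnant subjects will be excluded from further participation in trial and referred for appropriate follow up according to local practice" | No; the protocol notes that pregnancy may alter glucose metabolism |
| Consent withdrawn | Leaves the study | No, and it cannot be required |
| Missed capsules without intolerance | No removal rule | Yes, by the general Visit 6 text |

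The first two rows are the defect. Those women may be willing and able to attend, yet the text gives them only undated final assessments. The pregnancy and consent rows are different in kind and are not part of this point.

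**Step 2. The plan's own sample size (10.1, HOMA-IR).** Inputs: difference 0.700, SD 0.384, two-sided 0.05, power 95%. For a two-sample t-test with n per arm, the noncentrality is 0.700 / (0.384 × √(2/n)) on 2n − 2 degrees of freedom.

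- n = 9: 0.700 / (0.384 × 0.4714) = 3.87 on 16 df, power 95.2%. The stated 9 per arm reproduces.
- n = 8: power 92.3%, so 9 is the smallest number that reaches 95%.
- Inflation as stated: 9 × 1.40 = 12.6, rounded up to 13 per arm, 26 in total. This also reproduces.

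**Step 3. The margin for lost outcomes.** 13 − 9 = 4 women per arm. Power by number measured per arm, assuming the full 0.700 effect and no selection:

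| Measured per arm | Power |
|---|---|
| 13 | 99.4% |
| 9 | 95.2% |
| 8 | 92.3% |
| 7 | 87.8% |

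The planned losses already use up this margin. At the 40% in 10.1, 13 × 0.60 = 7.8 per arm remain. At the 50% in *Dropouts and withdrawals*, 13 × 0.50 = 6.5 remain. The disagreement between those two rates, and the inflation by multiplying by 1.40 where dividing by 0.60 would give 15 per arm, are separate matters.

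**Step 4. How many women are affected.** This cannot be computed. Section 10.1 attributes the 40% to loss to follow-up or unplanned pregnancy, neither of which is removal for intolerance or discretion. *Adverse Events (AE)* anticipates no adverse events in either arm. No other figure is given.

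**Step 5. What keeping these women does to power.** Assume that a share d of the vitamin D arm stops and has no effect left at week 24, and that all 13 per arm are measured. The mean difference becomes 0.700 × (1 − d). With SD 0.384:

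| d | Power |
|---|---|
| 0% | 99.4% |
| 10% | 98.0% |
| 20% | 94.6% |
| 30% | 87.7% |
| 40% | 76.3% |

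Allowing for the extra spread in a mixed active arm (variance 0.384² + d(1 − d) × 0.700², averaged with the placebo variance 0.384²), power is 88.7% at 20% and 61.9% at 40%. So the case for retention is not that it raises power. It gives an observed comparison of the groups as randomised.

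**The case against.** Several stronger readings are tempting, and the protocol does not support them.

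- A reader might infer that every woman who stops capsules is removed. The quoted rule needs intolerance leading to poor compliance. Pill counts are kept and Visits 4 and 5 record dosing changes. Section 10.3.1 also lists women not treated as intended separately from those with missing efficacy data, so imperfect takers can evidently stay.
- A reader might infer that final assessments happen on the day of leaving. Their place beside the return of capsules makes an exit visit the likely reading, but no date is stated.
- A reader might infer that no analysis could recover the loss. The observed value cannot be recovered, but baseline and early assessments would support imputation and sensitivity analyses under assumptions.
- A reader might take the words about vitamin D intolerance to mean removal only from the active arm. The trial is double blind, the same section also speaks of intolerance to study medication generally, and women on placebo can report it. Differential loss is possible but not shown.
- A reader might convert the 40% or 50% dropout into a count of obtainable outcomes lost. The reasons given for the 40% do not allow that.
- A reader might suppose that an early OGTT would be used as the 6-month value and would understate the effect. The protocol says neither, and gives no time course.

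The strongest objection is that collecting these values alone changes nothing, because 10.3.1 would discard them. That stands, and the fix has to answer it. It can also be said that silence about follow-up is not a prohibition. That is true, but exclusion from the trial is stated, and the general Visit 6 wording does not say that it reaches women who have been excluded. That the investigator holds discretion in one section and the study co-ordinator in another is administrative and no part of this point.

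**Conclusion.** The point holds in a limited form. The protocol treats stopping capsules for intolerance, or at staff discretion, as leaving the study, and it provides no week-24 OGTT, insulin or 25(OH)D for those women. A 6-month comparison of everyone randomised would need untestable missing-data assumptions for them.

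The number of women is unknown and may be close to zero. The importance comes from the size of the trial: 13 per arm against 9 required leaves 4 spare, before the losses that the plan itself expects. The conclusion rests on reading exclusion from the trial as ending scheduled visits. If the sponsor meant these women to attend at week 24, the text needs to say so. The protocol should be amended, because the omission cannot be repaired after the data are collected.

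**What to change.** In *Procedures for handling withdrawal*, *Adverse Events (AE)* and *Criteria for stopping subject treatment*, separate stopping study capsules from withdrawing consent. State that a woman who stops for intolerance, poor compliance or discretion, who has not withdrawn consent and is not pregnant, remains in follow-up and is invited to Visit 6 at week 24 for the scheduled OGTT, insulin and 25(OH)D. Record the date and reason for stopping. Keep exit assessments for women who refuse later contact, and label them as early.

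In 10.3.1, add an analysis of all randomised women that uses these week-24 values. Without it, the extra data would be dropped.

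This changes data collection and analysis only. It sets no rule on when anyone stops treatment. Visit 6 and its blood samples are already planned, so the cost is amendment wording and the effort of retaining a few off-treatment women. As Step 5 of the working shows, including them may dilute the estimated effect. That is a consequence of estimating the effect of assignment.

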### *Treatment and follow up of AE*

Treatment of any AE is at the sole discretion of the investigator who should follow up subjects with AE until the event has resolved, until the condition has stabilised, the subject is lost to follow-up, or the adverse events are otherwise explained. Appropriate medical care should be arranged for the patient. Abnormal tests should be repeated until they return to baseline levels or an adequate explanation of the abnormality has been found. Any follow up information should be reported as soon as it becomes available.

- - - - - Treatment of over-dosage

Significant overdose of Vitamin D occurs with very high intake. In adults, toxicity occurs with more than 50,000 IU/day of Vitamin D for several months.

Suspicion of overdose will be referred to study doctor for further assessment.

Unblinding will be done at discretion of study doctor to allow further management.

- - - - - Pregnancy

Vitamin D at dose of 4000iu/ day is safe in for maintainence or prevention of Vit D deficiency and recommended in pregnancy ^24^.

However, as the study involves use of placebo, subjects who are found to be pregnant during screening will be excluded from further participation of trial. Hormonal changes during pregnancy may also alter glucose metabolism and potentially interfere with accuracy of results.

Only patient with no active plan to get pregnant again within 6 months of study participation will be recruited. In the event of unplanned pregnancy after randomization, treatment of subject will be unblinded. Pregnant subjects will be excluded from further participation in trial and referred for appropriate follow up according to local practice.

# STUDY CONDUCT

## Study visits and procedures

Any deviation from the study procedures described below will be noted in study document

### *Screening visit*

Otherwise healthy women with previous GDM now 6 to 24 months post partum, who are not breastfeeding and has no plan to conceive again within 6 months from recruitment will be invited to participate in the trial.

All women will have screening assessment which includes:

- Obtain consent
- Subject's demography: date of birth/age, sex, race, height (cm) and weight
- Background and medical history
- Record of concomitant medications- patient taking medications that may interfere with outcome of vitamin D will be excluded- eg antiepileptic, antituberculosis and calcium supplement. intake of vitamin D is prohibited within 3 months prior to screening
- Assessment of inclusion/ exclusion criteria
- Clinical examination- including
  - Complete physical examination
  - Body weight (kg) and height (cm), no shoes in light clothing
  - Blood pressure will be measured in the sitting position after 5 minutes rest. 3 measurements will be taken with a 2 minute interval between measurements- average of 3 measurements will be recorded
- Blood investigations: UE/Creatinine/LFT/ Calcium/ phosphate/ fasting lipid profile/HsCRP/Urinary Microalbumin creatinine ratio and plasma 25 (OH) D level
- 75g oral glucose tolerance test- with measurement for glucose and insulin at 0, 30,90 and 120 mins

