# STUDY DESIGN

## Overall study design

The study consists of 2 phases: the first phase includes initial recruitment and screening. The second phase includes recruitment of selected individuals into the vitamin intervention trial.

The intervention trial is a prospective, randomized, double-blind, placebo controlled, parallel group trial to assess the efficacy of Vitamin D supplementation on blood glucose and markers of metabolic syndrome in women with Vitamin D insufficiency and previous Gestation Diabetes Mellitus. Study recruitment will cease when the pre determined number of subjects have been enrolled. Recruitment period for study is estimated to be 6 months

At least 44 subjects will be screened in order to recruit 26 subjects for the study.

**Visit 1: Screening:** Otherwise healthy women with previous GDM now 6 to 24 months post partum, who are not breastfeeding and has no plan to conceive again will be invited to participate in the trial.

All women will have screening assessment, which includes:

- Obtain consent
- Medical history – assessment of inclusion/ exclusion criteria
- Record of concomitant medications- intake of vitamin D will be prohibited within 3 months of screening
- Clinical examination- including
  - Blood pressure measurement- average of 3 readings (sitting)
  - BMI
  - Waist: Hip ratio
- Blood investigations: UE/creatinine, LFT, Calcium, lipid profile, HsCRP, Urinary microalbumin-creatinine ratio,—women with chronic renal or liver disease will be excluded
- 75g Oral Glucose tolerance test—with measurement for
  - Glucose and in at time 0,60,90 and 120 minutes—subject with OGTT showing fasting glucose > 7mmol/L and/or 2 hour glucose >11.1 mmol/L will be excluded from study
  - Insulin at time 0, 60, 90 and 120 minutes – only subjects with glucose and vitamin D level fulfilling inclusion criteria will have insulin sample send for measurement
- Blood tests for plasma 25(OH) D-
  - Subjects with level > 50nmol/L will be reassured and excluded from study
  - Subjects with level < 15nmol/L will be diagnosed with Vitamin D deficiency and excluded from study

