# EFFICACY & SAFETY ASSESSMENTS

## Assessment of efficacy

Efficacy of Vitamin D replacement will be assessed with parameters below:

- Primary criterion
  - Change in glucose metabolism as assessed by area under curve for glucose (AUCgluc) and insulin (AUC ins) post 75 g OGTT
  - Change in Insulin sensitivity index as calculated by HOMA –IR^28^
- Secondary criteria
  - Change in Insulin Sensitivity index as calculated by QUIKI^27^
  - Change in dynamic Insulin Sensitivity using OGTT Insulin Sensitivity (OGIS)^25,26^
  - Change in Beta cell function as evaluated by ratio of AUCins to AUCgluc^29^
  - Change in Blood pressure (BP), Body Mass Index (BMI) and Waist Hip Ratio (WHR)
  - Change in fasting lipid profile, HsCRP and urinary Microalbumin creatinine ration
  - Change in plasma 25-OH- Vitamin D level pre and post replacement

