### *8.1.5.Visit 6*

This is the final visit- all subjects will attend fasting and have

- Repeat clinical examination- including
  - Blood pressure measurement- average of 3 readings (sitting)
  - BMI
  - Waist: Hip ratio
- Repeat 75g Oral Glucose tolerance test—with measurement for
  - glucose and Insulin at time 0,60,90 and 120 minutes
- Repeat Blood tests for plasma 25(OH) D, calcium, phosphate, albumin, Fasting lipid profile, HsCRP and Urinary microalbumin creatinine ratio.

Study visits schedule and procedures are summarised in the table below:

|  | **Screening** | **Assessment of results (optional CRC visit)** | **randomization** | **Treatment** | | **End** | |
| --- | --- | --- | --- | --- | --- | --- | --- |
| **Visit** | **1** | **2** | **3** | **4** | **5** |  | **6** |
| **Timeline** | **-2 wks** | **-1 wk** | **0 +/-1 wks** | **8 +/-1 wks** | **16 +/-1 wks** |  | **24**  **wks** |
| **Procedures** |  |  |  |  |  |  |  |
| Check eligibility | X | X | X |  |  |  |  |
|  |  |  |  |  |  |  |  |
| Informed consent | X |  |  |  |  |  |  |
| Randomisation |  |  | X |  |  |  |  |
| Patient demographics & medical history | X |  |  |  |  |  |  |
| Clinical examination- incl BP/ WHI/BMI  Paffenburger physical activity score | X |  | X |  |  |  | X |
| Lab test:  UE/ Creatinine/ LFT  Calcium, phosphate and albumin  Fasting lipid profile  HsCRP  Urinary Microalbumin Creatinine Ratio  2 hour 75g OGTT with glucose and insulin | X  X  X  X  X  X |  |  | X |  |  | X  X  X  X |
| Plasma 25(OH) D | X |  |  |  |  |  | X |
| Urine Pregnancy test |  | X |  |  |  |  |  |
|  |  |  |  |  |  |  |  |
| Report AE and SAE |  |  | X | X | X |  | X |
| Dispense study treatment |  |  | X | X | X |  | X |
| Complete relevant section of CRF | X |  | X | X | X |  | X |

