## Sample handling and analysis

## Collection

105 ml of blood will be drawn for through the 6 months study duration- consisting of:

50 ml of blood will be drawn at screening visit (wk -2) for –

UE, creatinine, LF, Calcium and phosphate, fasting lipid profile, HsCRP (5ml)

plasma 25(OH) vit D ( 5ml)

OGTT at time 0, 60,90 and 120 min for glucose ( 20ml) and insulin ( 20ml)

5 ml of blood will be drawn at visit 4 (wk 8) for-

Calcium, phosphate and albumin (5 ml)

50ml of blood will be drawn at study completion ( wk 24) for-

Calcium, phosphate and albumin, fasting lipid profile, HsCRP (5ml)

plasma vit D ( 5ml),

OGTT at time 0, 60,90 and 120 min for glucose (20ml) and insulin ( 20ml)

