# 10 STATISTICAL METHODS

## 10.1 Sample size and power considerations

Using AUC insulin:
By using nQuery Advisor version 6.01, from paper written by Gedik et al (Effects of vitamin D deficiency and repletion on insulin and glucagon secretion in man ^)16^, a sample size of 4 will have 95% power to detect a difference in means of -4.610 (e.g. the First condition mean, µ1, of 9.090 and a Second condition mean, µ2, of 13.700), assuming a standard deviation of differences of 1.200, with a 0.050 two-sided significance level. By adding 40% dropped out patient in case of lost to follow up unplanned pregnancy, the total sample for 2 arms (placebo and treatment group) treatments is 11 patients.

Using HOMA-IR:
By using nQuery Advisor version 6.01, from paper written by Von Hurst et al (Vitamin D supplementation reduces insulin resistance in South Asian women living in New Zealand who are insulin resistant and vitamin D deficient - a randomised, placebo-controlled trial )^31^, a sample size of 9 will have 95% power to detect a difference in means of 0.700 (e.g. the differences between Group 1 mean, µ1, of 0.800 and a Group 2 mean, µ2, of 0.100), assuming that the common standard deviation is 0.384, with a 0.050 two-sided significance level. By adding 40% dropped out patient in case of lost to follow up or unplanned pregnnacy, the total sample for 2 arms (placebo and treatment group) treatments is 26 patients (13 patients for each arms).

Since the study will be using both efficacy analysis, higher sample calculated using HOMA-IR was chosen as reference ie 26 subjects required for study.

Green et al (Vitamin D status and its association with parathyroid hormone concentrations in women of child-bearing age living in Jakarta and Kuala Lumpur)^15^ found 60% of population to have 25 (OH) Vit D of < 50nmol/L. Assuming a similar prevalence exist in our population, we thus expect to screen at least 44 women to recruit 26 subjects for the study.

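### The screening-visit text samples the baseline OGTT at 0, 30, 90 and 120 min, but the rest of the protocol gives 0, 60, 90 and 120 min at both baseline and week 24

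*Protocol*

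**What the plan says.** Under Study Conduct, the Screening visit text specifies "75g oral glucose tolerance test- with measurement for glucose and insulin at 0, 30,90 and 120 mins". Later in the same section, 8.1.5.Visit 6 specifies "glucose and Insulin at time 0,60,90 and 120 minutes" for the final test.

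Two other places describe the screening test and disagree with the first of these. Overall study design, Visit 1, gives "Glucose and in at time 0,60,90 and 120 minutes" for glucose and "Insulin at time 0, 60, 90 and 120 minutes" for insulin. The Collection list under Sample handling and analysis gives "OGTT at time 0, 60,90 and 120 min for glucose ( 20ml) and insulin ( 20ml") for the screening draw, and the same times again for week 24. Overall study design, Visit 6, also gives 0, 60, 90 and 120 min. The visit schedule table lists the OGTT at screening and at the final visit but states no times, so it does not settle the matter.

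The endpoints that rest on these samples are in Assessment of efficacy. One primary criterion is "Change in glucose metabolism as assessed by area under curve for glucose (AUCgluc) and insulin (AUC ins) post 75 g OGTT", and a secondary criterion is "Change in Beta cell function as evaluated by ratio of AUCins to AUCgluc". The other primary criterion is change in HOMA-IR.

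**The concern.** The AUC criteria are changes from baseline, and the schedule contains only one OGTT before treatment. If the Study Conduct text is carried out as written, the baseline AUC includes a 30-minute value and no 60-minute value, while the final AUC includes a 60-minute value and no 30-minute value. The two areas are then not the same quantity, and their difference mixes any real change with a sampling artefact that depends on the shape of each woman's curve. The AUCins/AUCgluc ratio inherits the problem from both its parts. A baseline time point that was not drawn cannot be recovered once treatment has started.

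**Working it through.** **Places side by side**

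| Place in protocol | Visit | Times (min) |
|---|---|---|
| Overall study design, Visit 1 | Screening | 0, 60, 90, 120 |
| Study Conduct, Screening visit | Screening | 0, 30, 90, 120 |
| Collection, wk −2 | Screening | 0, 60, 90, 120 |
| Overall study design, Visit 6 | Week 24 | 0, 60, 90, 120 |
| Study Conduct, 8.1.5.Visit 6 | Week 24 | 0, 60, 90, 120 |
| Collection, wk 24 | Week 24 | 0, 60, 90, 120 |

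One entry differs from the other five. The blood volumes (20 ml for glucose and 20 ml for insulin) fit either set of four draws and do not help to choose between them.

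**The plan's own figure.** The protocol states no AUC value that depends on the sampling times. Its total of 26 rests on HOMA-IR, for which section 10.1 says that "a sample size of 9 will have 95% power to detect a difference in means of 0.700". With SD 0.384 and two-sided 0.05, a two-sample t-test gives 95.2% power at 9 per arm and 92.3% at 8, so the 9 is reproduced. No OGTT time after 0 enters that calculation.

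**Effect of the mismatch.** The protocol does not name the AUC rule, so I assume the trapezoidal rule. The weights in minutes are:

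- 0/30/90/120: 15, 45, 45, 15
- 0/60/90/120: 30, 45, 30, 15

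The 30- and 60-minute values carry the same weight, 45. What differs is the time sampled and the weights at 0 and 90 min. For a curve identical at both visits, final minus baseline is

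(30 − 15)G0 + 45(G60 − G30) + (30 − 45)G90 = 45(G60 − G30) − 15(G90 − G0).

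This is generally not zero. With the same times at both visits it is exactly zero.

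**Illustration.** The documents give no curves, so those below are assumed (values at 0/30/60/90/120 min; glucose in mmol/L, insulin in arbitrary units). Each is unchanged between visits.

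| Assumed curve | Baseline AUC (30-min text) | Final AUC | Apparent change |
|---|---|---|---|
| Glucose, early peak: 5/9/8/7/6.5 | 892.5 | 817.5 | −75 (−8.4%) |
| Glucose, late peak: 5.5/9/11/10/9 | 1072.5 | 1095 | +22.5 (+2.1%) |
| Insulin, early peak: 10/80/60/45/35 | 6300 | 4875 | −1425 (−22.6%) |
| Insulin, late peak: 10/50/90/85/70 | 7275 | 7950 | +675 (+9.3%) |

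Check of the first row by the formula: 45(8 − 9) − 15(7 − 5) = −45 − 30 = −75.

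A second set of assumed curves gave −6.1% to +0.3% for glucose and −17.6% to +3.0% for insulin: the same pattern, somewhat smaller.

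For the ratio AUCins/AUCgluc, pairing the early-peak curves gives 6300/892.5 = 7.06 against 4875/817.5 = 5.96 (−15.5%). Pairing the late-peak curves gives 7275/1072.5 = 6.78 against 7950/1095 = 7.26 (+7.0%).

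**Effect on the randomised comparison.** Write B for baseline AUC and F for final AUC. The expected between-arm difference in change is

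{E[F | vitamin D] − E[F | placebo]} − {E[B | vitamin D] − E[B | placebo]}.

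The screening test is done before randomisation, so the second bracket is zero in expectation whichever times were used. The first bracket uses the same times in both arms. The artefact therefore drops out in expectation, although it varies from woman to woman and stays in the individual changes.

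**The case against.** The strongest reply is that this is a drafting slip. For the screening visit itself, the design section and the Collection list both give 0, 60, 90 and 120 min, and the Study Conduct text is the only exception. That is a fair reading, and it makes the harm conditional on someone working from that text. It does not remove the contradiction. Study visits and procedures says that deviations from what follows it will be noted, which gives the Study Conduct text some operative standing, and nothing in the protocol says which place prevails.

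It can also be said that the percentages rest on invented curves and describe shifts within one woman, not an effect on the treatment comparison. Both statements are correct. The formula does not depend on the curves, but the sizes do, and the added variance cannot be quantified from the document.

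A reader might infer that the mismatch biases the treatment contrast, for instance if staff follow different places in the text or if vitamin D alters the shape of the curve. The document does not support that. The baseline times are fixed before allocation and cannot depend on arm. Treatment can alter only the final curve, which every statement measures at the same times in both arms. The per-protocol exclusions in section 10.3.1 could unbalance the arms, but that is a separate matter and does not arise from the sampling times.

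**Conclusion.** The concern holds as an internal contradiction on the baseline of a primary criterion. If the Screening visit text is followed, change in AUC is computed from unlike sets of times, and an unchanged curve shows a spurious change of 45(G60 − G30) − 15(G90 − G0). That is roughly −8% to +2% for glucose and −23% to +9% for insulin, on the trapezoidal rule and the assumed curves. The consequences are misleading within-arm change, a baseline less comparable with the final value, and in general added shape-dependent noise in a trial of 13 per arm. Bias in the randomised comparison is not among them.

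HOMA-IR is unaffected because it uses fasting values, and time 0 is in both sets of times. The sample size of 26 rests on HOMA-IR and is also unaffected. The screening glucose limits use the fasting and 2-hour values, which both sets include, so classification by the OGTT does not change either. The protocol does not give the OGIS formula, so I draw no conclusion about it.

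**What to change.** Reconcile the Screening visit text under Study Conduct with Overall study design (Visits 1 and 6), 8.1.5.Visit 6 and the Collection list, so that glucose and insulin are drawn at the same four times at baseline and at week 24. The times stated everywhere else are 0, 60, 90 and 120 min. Adding the times to the OGTT row of the visit schedule table would help to prevent a recurrence.

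The cost is one corrected line, with no extra samples, blood, visits or subjects. It should be done before the first screening OGTT, because a missed baseline time cannot be drawn later. A rule to compute AUC only from times common to both visits is not needed once the line is corrected. Applied to a woman already sampled at 0, 30, 90 and 120 min, it would leave only 0, 90 and 120 min and a 90-minute gap.
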